##### Environment and context

The intervention activities will take place indoors and outdoors, both within and outside of the preschool area (e.g., using a nearby forest, beach, park, playground, etc.). Because more time spent outdoors is associated with increased PA (Bingham et al., 2016; Driediger et al., 2018), and better cognitive and behavioral development (Ulset et al., 2017), preschools will be encouraged to spend ample time outdoors each day. Through the use of various environments, children will have access to play areas with a variety of surfaces (e.g., floor, grass, sand, bark, mud, dry, wet, snow, ice, etc.) and terrain (flat, hilly, rocks, trees, etc.) to support the variability of practice and optimal stimuli of motor and cognitive development (Pesce et al., 2019). The environment, both inside and outside, will be enriched by portable equipment to encourage various movements, including hula-hoops, balls of different sizes and weights, bean bags, sensory slices, cones, and hurdles. Such portable play equipment has been shown to increase MVPA (Driediger et al., 2018; Määttä et al., 2019). Furthermore, equipment such as dice, letters, shapes, and pictures will be provided to incorporate learning goals through physically active play.

Most of the intervention activities will take place in groups of children, facilitating interaction between peers and with staff. Socially oriented physically active play and games are important for the development of socioemotional competence and hence friendships in the early years. Furthermore, physically active play can affect social connectedness and a sense of belonging (Bailey, 2017). Therefore, promotion of such activities is especially important for children showing the least developed social skills (Bailey, 2017).

##### The “physical activity of moderate-to-vigorous intensity” component

The specific amount of PA needed for optimal development and health in the early years is unclear (Timmons et al., 2012; Carson et al., 2017). More intense PA appears to be most favorable to health (Carson et al., 2017), and cognitive and psychosocial development (McNeill et al., 2018). In Norway and internationally, it is recommended that young children spend at least 60 min/day in MVPA (Tetens et al., 2014; World Health Organization [WHO], 2019). There is general concern about low PA levels internationally (Bornstein et al., 2011; Driediger et al., 2018; Truelove et al., 2018), and recent evidence shows that only 55% of 3- to 5-years-old in Norway achieve this amount of MVPA (Nilsen et al., 2019c).

Beyond physical health, a sufficient dose of PA is also hypothesized to be of importance for cognition, with executive function being the most promising outcome (Tomporowski et al., 2008). The general physiological and metabolic mechanisms that are related to aerobic fitness (Best, 2010) are suggested as pathways for how PA affects executive functions (The Aerobic Fitness Hypothesis) (Howie et al., 2015; Howie and Pate, 2018). Research with 9- to 10-years-old children has shown that higher-fit children have better executive function, greater activity in brain regions important for attention and memory, and a positive change in gray matter volume in brain regions implicated in learning (Chaddock et al., 2011). In preschool children, Niederer et al. (2011) found that aerobic fitness predicted attention 9 months later, but such relationships are scarcely investigated in young children.

##### The “Motor challenging physical activity” component

Learning to move is essential for PA, and during the early years, children acquire competence in diverse fundamental movement skills, such as locomotion and object control (Stodden et al., 2008). Motor competence has been suggested to be a primary underlying mechanism that promotes engagement in PA, both acutely and over the long-term. A conceptual model by Stodden et al. (2008) proposes a synergistic relationship among motor competence, perceived motor competence, PA, physical fitness, and weight status. During the early years, the child’s perception of their motor competence is especially important, as children with high perceived motor competence are more persistent and engaged in various activities. Importantly, their perceived motor competence might be weakly correlated to their actual motor competence (Stodden et al., 2008). As such, an intervention aiming to improve motor competence might benefit from building children’s perceptions of their motor competence. Moreover, both AGT and SDT emphasize perceived competence as an important psychological factor (Robinson et al., 2015), which may act as a mediator between actual motor competence and actual/future PA, as well as various developmental outcomes. Robinson et al. (2015) reviewed the proposed links in the conceptual model by Stodden et al. (2008) and concluded that motor competence and PA are weakly to moderately associated in early and middle childhood. This is consistent with results from a large Norwegian study in preschoolers, which extends these results by showing that the association pattern between PA and motor competence is characterized particularly by vigorous intensities (Nilsen et al., 2019a).

Importantly, motor competence will likely not be optimally stimulated through naturally occurring behaviors and thus needs to be taught (Stodden et al., 2008; Robinson et al., 2016). Furthermore, to optimally promote motor competence, it is important to provide challenging activities that keep the children on a positive trajectory of learning and maximize motivation and engagement (Robinson et al., 2015). Consistent with the Challenge Point Framework (Guadagnoli and Lee, 2004), the ACTNOW intervention seeks to adapt intervention activities that are developmentally appropriate and individually adapted in order to meet each child’s optimal challenge point.

Providing children with challenging motor tasks may also be a viable way to affect their executive functions, through increased cognitive engagement (Best, 2010). Motor tasks that are novel or not automatized require the involvement of executive functions (Diamond, 2000; Guadagnoli and Lee, 2004; van der Fels et al., 2015; Pesce et al., 2019), and an interrelation between the brain structures important for motor skills (cerebellum) and the structures important for executive functions (the prefrontal cortex) has been described (Diamond, 2000). The interrelation between these structures is evident by their co-activation during motor and cognitive tasks, their similar developmental timetable, and their common underlying processes such as, for example, planning (Diamond, 2000; Roebers et al., 2014; van der Fels et al., 2015). As such, practicing challenging motor tasks may lead to specific adaptation in brain areas (prefrontal cortex) that support executive functions (Best, 2010). The importance of meeting children’s optimal challenge point to affect their executive functions has been highlighted in the literature (Pesce et al., 2013, 2019; Tomporowski et al., 2015; Diamond and Ling, 2016). Some evidence also exists for added value of motor skill tasks to executive functions beyond the effects of MVPA (Chang et al., 2013; Koutsandreou et al., 2016).

##### The “Cognitively engaging physically active play” component

Increasing the complexity of the PA context through structured games or active play, which engage core executive functions, is a viable way to increase the cognitive demands of PA and hence promote executive functions (Best, 2010; Pesce, 2012; Tomporowski et al., 2015). It has been suggested that engaging executive functions through play can confer benefits to other domains where executive functions are needed (Best, 2010). In group games, the learning environment is in constant change, and the child needs to adapt his/her movement in relation to these dynamic changes. In doing so, the child uses his/her executive functions.

Furthermore, manipulation of activities can increase demands on executive functions. Such manipulation is important, as executive functions need to be continuously challenged in order to be improved (Tomporowski et al., 2015; Diamond and Ling, 2016). In regard to the optimal Challenge Point Framework (Guadagnoli and Lee, 2004), the cognitive load of an activity needs to be tailored to each child. Previous research has shown that children with different abilities may benefit from different activities. For example, Pesce et al. (2013) showed that a cognitively enriched PA program facilitated development of attention in typically developing children (aged 5–10) but not in children with Developmental Coordination Disorder.

##### The “Physically active learning” component

The physically active learning component will integrate PA with different learning areas in *The Norwegian Framework Plan for Kindergartens* (Norwegian Directorate for Education and Training, 2017). Learning areas in the Framework plan are: (*1) communication, language, and text; (2) body, movement, food, and health; (3) art, culture, and creativity; (4) nature, environment, and technology; (5) quantity, spaces, and shapes; (6) ethics, religion, and philosophy; and (7) local community and society* (Norwegian Directorate for Education and Training, 2017). The physically active learning component derives from the research fields of both acute exercise and embodied cognition. From the exercise and cognition field, the physiological effects of acute PA might facilitate the learning process of academic content by increased arousal. For example, acute PA of a sufficient intensity/dose can raise the concentration of neurotransmitters and cortisol to levels that have positive effects on cognition (McMorris and Hale, 2012; Koutsandréou et al., 2016). Bouts of PA with academic content have shown improved on-task behavior in school settings (Mahar et al., 2006; Grieco et al., 2016). As such, gross motor MVPA coupled with academic content will be promoted in the intervention.

From the perspective of embodied cognition, the relevance of PA for the academic content is of importance. Gesturing or PA that are tightly coupled to the academic content might off-load demands on working memory during learning, through experiencing complementary content through several senses that use different memory traces. As such, it is hypothesized that the learning trace will be of higher quality, and as such better learned (Mavilidi et al., 2018b). Some of the intervention activities will be tightly coupled to the learning content, for example, by forming letters, shapes, and figures with the children’s bodies. Several studies in preschool children have successfully used task-relevant PA to learn academic content in, for example, language/literacy (Kirk et al., 2014; Mavilidi et al., 2015), numeracy (Schmidt et al., 2015), and science (Mavilidi et al., 2017).

#### The Preschool Level

The staff professional development is described in Table 2. As described above, a flexible intervention that includes co-creation and continual improvement with staff is recommended to facilitate sustainable change in educational contexts (Routen et al., 2017). The ACTNOW intervention will therefore be adjusted to the needs and resources in each preschool. Alongside the involvement of directors and teachers in the professional development, the research group will work in partnership with each preschool and its entire staff to ensure support and commitment, not only among those enrolled in the professional development. As recommended by the literature on health promotion assessment and interweaving (Springer et al., 2017), the process among staff will begin by involving all in an analysis of the preschool’s existing PA policies and practices as well as an assessment of staff and children’s needs and resources related to PA, and thus their readiness for change. Based on the assessment, staff will develop a written PA policy with set priorities and objectives, which will incorporate both intervention levels, including the four core components for children. Depending on each preschool’s current practice, the elements of the intervention will add to, extend, and/or integrate with and improve existing activities in line with the Theory of Expanded, Extended, and Enhanced Opportunities (Beets et al., 2016), which corresponds with concepts of organizational learning (Nonaka, 1994; Wells, 1999; Moilanen, 2005). In collaboration with the researchers, the next phase will involve developing strategies for the implementation and integration of the new policy and practices into the preschool’s daily practice (Fitzgerald and Theilheimer, 2013; Heikka et al., 2019). The final phase will consist of monitoring and evaluation, revision, and learning. Given that the principal/director in educational contexts plays a pivotal role in the development and adoption of interventions (Roberts et al., 2015), the preschool director, together with the teachers taking part in the professional development, will be in charge of leading the rest of the staff through the process (Boe and Hognestad, 2017). The researchers will support the implementation process through email, telephone, and visits to each preschool during the intervention period. In addition, a customized website with teaching resources will be provided.

**TABLE 2 T2:** Overview of the professional development (preschool level).

Structure	The professional development will be structured as a 15-credit continuing education module at a master’s degree level delivered over 7 months. However, the staff can choose whether they will complete the exam and achieve credits or complete the professional development without credits. Seminars and webinars total 6 days face-to-face (3 days on campus and 3 days locally in each preschool) and multiple webinars, amounting to approximately 50 h in total.

Requirements for participation	We will request the preschool director and minimum one teacher from each classroom to participate. Skilled workers/assistants and others will primarily be involved locally through the processes initiated and facilitated by the director and teacher(s). Yet, preschools can choose to let skilled workers/assistants participate in the professional development, depending on their needs and resources.

Aims/content	The aims of the professional development are to increase the preschool directors’ and teachers’ competences regarding 1. the importance of physically active play and its relevance for child development, and how to integrate more physically active play (the core components) into the preschool’s practice; and 2. planning and implementation of interventions/changing practice, and thus facilitate the ACTNOW implementation process within the entire preschool and its staff.

Process	The professional development has three phases **Phase 1: Setting the stage (2 months)** The professional development will start by an intensive 2-day face-to-face seminar. One part of the seminar will focus on the intervention at the child level, with both practical and theoretical sessions regarding the four core components, as well as general topics on PA and physically active play, motor competence, cognitive development, and didactics. The other part of the seminar will focus on the process of the development work among the preschool staff. The seminar will be followed by a 1-day visit to each preschool by a member of the research group. This visit will include a half-day observation of practice and a 2 h staff meeting, planned by the preschools, including discussion of each preschool’s specific PA practice, contextual factors, needs, resources, etc. During this first phase, the directors/teachers will be responsible for drafting a model on how to integrate the four core components into their daily practice, which will be subject to feedback and discussion in an individual webinar with the research group.
	**Phase 2: Customize the intervention for sustainability (3 months)** The second phase of the professional development will focus on the implementation of each preschool’s intervention model at the child level. Based on the initial experiences and discussions in Phase 1, each preschool model will be revised, if necessary, and further developed to meet with the preschool practice and the prescribed intervention dose. During this second phase, multiple webinars will be given to extend the lectures and discussions in Phase 1. A group discussion will be arranged, where participants and the research group meet to share the preschools’ experiences regarding the implementation process.
	**Phase 3: Reflect on and evaluate the intervention (2 months)** The third phase of the professional development will focus on reflection and evaluation of the changed preschool practice regarding the implementation of the preschool’s intervention model. Multiple webinars will be given, in addition to a 1-day visit in each preschool, with a new half-day observation, followed by a joint reflection in the whole staff group about the developmental work and (hopefully) changed practices. The professional development will end with a final full-day session of experience sharing among all intervention preschools, focusing on lessons learned and the way forward.

### Protocol and Randomization

ACTNOW will have two waves involving different cohorts, the first running from August 2019 to June 2021, and the second from August 2020 to June 2022 (Figure 3). The professional development provided in Wave 2 will be adjusted based on experiences and findings from Wave 1. Data collection will have three main stages; pre-testing performed before randomization, 7-month follow-up performed at the end of the professional development, and 18-month follow-up performed 1 year after staff have completed the professional development. In addition, process evaluation measures will be taken throughout the study.

**FIGURE 3 F3:**
[figure not shown]
Flow chart of the study.

We will cluster randomize at the preschool level, since we regard delivery of the intervention on the preschool level the only practical approach. A third party ([name], Norwegian School of Sport Sciences) will randomize ≈ 60 preschools to the intervention group (≈ 30 preschools) or the standard of care control group (≈ 30 preschools). Randomization will be done separately in the two study waves after completing recruitment and before initiating baseline data collection using a random number generator (Stata/SE 15.1, StataCorp LLC, College Station, TX, United States). We will use block randomization (randomly chosen block sizes of 4 and 6) and a 1:1 ratio for the two intervention arms. Blinding of participants and preschools is not possible due to the nature of the experiment. To limit potential biases, the fewest possible assessors involved in project management, data collection, and statistical analysis will have knowledge about the group assignment and the study hypotheses.

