##### Anthropometry and demography

We will assess children’s body mass, height, and waist circumference according to the PREFIT battery (Ortega et al., 2015). Body weight will be measured to the nearest 0.1 kg using an electronic scale (Seca 899, SECA GmbH, Hamburg, Germany), and height will be measured to the nearest 0.1 cm with a portable stadiometer (Seca 217, SECA GmbH, Hamburg, Germany). Body mass index (kg/m^2^) is calculated and children classified as normal weight, overweight, or obese based on criteria proposed by Cole et al. (2000). Waist circumference will be measured twice to the nearest 0.1 cm at the level of the umbilical zone. Demography includes the variables socioeconomic status (parents’ education and income), children’s and parents’ origins, children’s birth weights, parents’ weight status, and parents’ PAs, and they will be measured by parent questionnaires.

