##### Socioemotional health, self-regulation, executive function, and learning

We will adapt several validated tests to examine different aspects of socioemotional health, self-regulation, executive functions, and learning. Yet, there exists little agreement on the optimal measures and their configuration for capturing important aspects of early cognitive development (Garon et al., 2008; Howard and Melhuish, 2017).

To assess **socioemotional health,** we will ask the teachers to fill out the Strengths and Difficulties Questionnaire (SDQ) for each child. The SDQ is a brief measure of psychosocial strengths and problems in 3- to 16-years-old children. The SDQ asks about 25 attributes (10 positive, 14 negative, and 1 neutral) divided between five subscales of five items each: (*1) Emotional Symptoms Scale; (2) Conduct Problems Scale; (3) Hyperactivity Scale; (4) Peer Problems Scale;* and (*5) Prosocial Scale*. All but the last scale are also summed to give a total difficulties score. SDQ uses a 3-point Likert scale to indicate the extent to which each attribute applies to a child (“not true,” “somewhat true,” or “certainly true”) (Goodman, 1997, 2001). The construct validity of the SDQ has been demonstrated in several studies (Goodman, 2001; Stone et al., 2010; Mieloo et al., 2012), and the reliability and validity of the SDQ has been shown to be satisfactory (Goodman, 2001; Stone et al., 2010). The teacher version of the SDQ has shown both higher internal consistency and test-retest reliability compared to the parent version for preschool and schoolchildren (Stone et al., 2010; Mieloo et al., 2012).

**Self-regulation** will be assessed both by teacher-report and a structured observation (direct measure) of a child’s performance. Teachers will be asked to fill out the 33-item Child Self-regulation and Behavior Questionnaire form from the Early Years Toolbox (EYT) (Howard and Melhuish, 2017). The Child Self-regulation and Behavior Questionnaire generates subscales on cognitive, behavioral, and emotional self-regulation, in addition to sociability, prosocial behavior, externalizing and internalizing problems, which overlaps with the SDQ. Each item asks the teacher to evaluate the frequency of target behaviors of each child on a scale from 1 (not true) to 5 (certainly true). The subscales of the questionnaire have been shown to be reliable in preschoolers (Howard and Melhuish, 2017).

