## Ethics Statement

The study is approved by the Institutional Ethics Committee and the Norwegian Centre for Research Data (reference number 248220). ACTNOW will study children, a vulnerable group that is unable to give valid consent. We will obtain written informed consent from each child’s parent/guardian prior to testing. Children will be informed about the study procedures on their premises. We will perform all child testing in close collaboration with preschool staff to provide a safe environment for children. Testing will be terminated if a child expresses discomfort. Similar to children/parents, staff will provide written informed consent, specifically tailored to the research activities they participate in, prior to all testing. Procedures and methods will conform to the ethical guidelines defined by the World Medical Association’s Declaration of Helsinki and its subsequent revisions (World Medical Association [WMA], 2017).

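### The protocol gives two opposite orders for baseline testing and randomization; under one of them teachers may know their arm when they rate children at baseline

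*Protocol article*

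**What the plan says.** The Protocol and Randomization section of the protocol article describes three main stages of data collection. The first is "pre-testing performed before randomization"; the other two are the 7-month and 18-month follow-ups. In the same section, in the paragraph after Figure 3, the timing of the draw is given as: "Randomization will be done separately in the two study waves after completing recruitment and before initiating baseline data collection". A third party performs the randomization.

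That paragraph also says: "Blinding of participants and preschools is not possible due to the nature of the experiment". For assessors it offers a limit rather than a bar: "the fewest possible assessors involved in project management, data collection, and statistical analysis will have knowledge about the group assignment".

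Two of the baseline instruments are completed by preschool teachers. For socioemotional health, "we will ask the teachers to fill out the Strengths and Difficulties Questionnaire (SDQ) for each child". For self-regulation, "Teachers will be asked to fill out the 33-item Child Self-regulation and Behavior Questionnaire form". The Analysis Plan (Primary aim) places both constructs within children's cognition, which it treats as the main outcome, and tests intervention effects as time-by-group interactions. The only other statement on opening the allocation is under Data Management. It concerns locking the database at the follow-ups and does not cover baseline or disclosure to preschools.

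**The concern.** A reader cannot tell whether baseline data are collected before or after preschools are allocated. In a cluster trial with unblindable preschools and staff-completed ratings, this decides whether the baseline of part of the main outcome is protected from knowledge of arm.

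If teachers know they are about to receive the professional development, or know they are not, their first ratings of the children may move with that knowledge. The baseline value is one half of every change contrast, so a shift of this kind would enter the effect estimate. Adjusting for baseline would reduce the shift but not remove it, because the covariate is itself the affected measurement.

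**Working it through.** **The two statements side by side.**
- The stage list puts baseline testing first and randomization second. The word used there is pre-testing, but the other two stages are the follow-ups, so it can only mean baseline.
- The paragraph after Figure 3 puts recruitment first, randomization second and baseline data collection third.

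These are opposite orders for the same two events in the same section. The Data Management rule does not resolve them, because it covers only the follow-ups. The flow chart (Figure 3) was not available for this check.

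**Who could be affected under the second order.**
- *Teacher questionnaires* (SDQ, Child Self-regulation and Behavior Questionnaire): the rater works in the allocated preschool. No withholding of the allocation until baseline is described, so the rater may know the arm.
- *Observer-scored tests* (motor skills, Head-Toes-Knees-Shoulders): less exposed, because assessors' knowledge of the assignment is to be limited, though it is not excluded.
- *Accelerometry and the tablet tasks*: less exposed than teacher reports.

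**How a baseline shift carries through.** Work in SD units. Let d be the true effect, x the rating shift in one arm (here the intervention arm) at baseline, and y the shift in the same arm at follow-up. Randomization makes the expected true baseline difference zero.

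Change contrast (time-by-group interaction):

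(follow-up difference) − (baseline difference) = (d + y) − x

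- Shift at baseline only (y = 0): d − x. The bias has size x.
- Same shift at both times (y = x): d. The shift cancels.

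Baseline-adjusted contrast with slope b:

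(d + y) − b·x

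With equal SDs at the two times (assumption), b is about the correlation of repeated measurements. The sample-size paragraph under Participants gives this as 0.6-0.7.
- Shift at baseline only: d − 0.6x to d − 0.7x. The bias has size 0.6x to 0.7x.
- Same shift at both times: (1 − 0.6)x = 0.4x down to (1 − 0.7)x = 0.3x remains.

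The documents give no value for x, so the result stays in terms of x.

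**The case against.** The strongest reply is that the second statement fixes when the draw is made, not when anyone is told. A reader might infer that, under that order, teachers and parents give baseline data knowing their arm. The text does not say so. The remark that blinding is impossible refers to the nature of the intervention and is compatible with a draw made early and disclosed late. This stands, and it limits the claim to *may know*. It does not remove the claim, because no such withholding is described.

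A reader might also infer that parental consent follows allocation, since the Ethics Statement ties it only to the time before testing ("parent/guardian prior to testing"). But the draw comes after recruitment is completed, and both the Abstract and the Participants section speak of recruiting children as well as preschools. On that usage, children are enrolled before allocation under either order. The consent risk arises only if completed recruitment means preschools alone.

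Two further extensions are not supported:
- *The MOVERS room rating* is made in all rooms at baseline but afterwards used only in the intervention group, and is analysed for change over time. It has no between-arm effect for a baseline shift to enter.
- *Parent-reported data*, such as the demographic variables ("they will be measured by parent questionnaires"), screen time and the sleep questionnaire, are not among the outcomes named as main or secondary in the Analysis Plan.

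Nor can the bias be stated as a fraction of the effects the trial is powered to detect. That would need a value for x, which the documents do not supply. It would also need the shift to be absent at follow-up, and the same teachers could carry it forward.

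None of this tells the reader which order applies.

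**Conclusion.** The contradiction is plain and rests on the wording alone: one section gives both orders, and no visible text reconciles them. The consequence is conditional. It needs the second order to be followed, the allocation to reach teachers before they complete the baseline questionnaires, and their ratings to shift by arm as a result.

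If so, two teacher-rated instruments within the main outcome are exposed. The bias in the change contrast equals the shift when that shift is absent at follow-up, is about 0.6 to 0.7 of it with baseline adjustment, and is zero in the change contrast when the shift persists equally. The adjusted figures assume similar SDs at both times and the protocol's own correlation. The text should be corrected because it concerns the order of allocation and the correction is simple.

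**What to change.** State one order in both places: complete child enrolment and parental consent, then all baseline child tests and teacher questionnaires, and only then have the third party release the allocation. Correct the sentence that puts randomization ahead of baseline data collection.

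If logistics require an earlier draw, say that the third party withholds the result from preschools, parents and assessors until that preschool's baseline is complete. In either case, state when the allocation is disclosed and whether completed recruitment includes the children.

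The cost is a change of wording and control over the timing of release. A third party already performs the randomization, and no participants, measurements or analyses are added.
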